### Data collection and data management

#### Data collection

All eligible patients who provide informed consent will be included in a secure online database using Castor EDC. Clinical data will be collected through e-CRFs completed by the treating gynaecologist at the participating centre. The coordinating investigator will review all entered data to ensure completeness and consistency. Participants will complete validated online questionnaires via Castor EDC at baseline (prior to treatment, if applicable), and at 6 months, 2 years and 5 years after diagnosis.

#### Collected variables

Baseline characteristics include age, body mass index, type of physical complaints, medical history, use of medication and Eastern Cooperative Oncology Group (ECOG) performance status (known as WHO performance score).^24^ Diagnostic measurements include imaging details (date of imaging, results of gynaecological examination and advanced imaging), biochemical laboratory results and histopathology results of endometrial biopsies and surgical specimens. Regarding the histopathological examination, the following data will be obtained: the histomorphological characteristics, immunohistochemistry staining on mismatch repair proteins (MMR) and p53 mutation and results of molecular diagnostics (MSI test, p53 mutation analysis, POLE mutation analysis). Treatment details include details on the surgical treatment (date, type of surgical procedure (hysteroscopy, hysterectomy with/without salpingo-oophorectomy, staging procedure, cytoreductive surgery), perioperative findings (dissemination of disease and FIGO stage of disease), and perioperative complications) and details on administered adjuvant therapy (date, duration and type/regimen of adjuvant therapy). Given anticipated changes in FIGO and WHO terminology, all cases will be stored with raw histopathology and molecular data, allowing for retrospective reclassification according to future systems. Follow-up data will be collected at 6 months, 2 years and 5 years after diagnosis and include clinical status, symptoms, QoL, evidence of disease recurrence and disease-related or unrelated death.

#### Data management

This research protocol adheres to the principles and requirements of the Dutch implementation of the EU General Data Protection Regulation (GDPR). All data collected during the study will be processed lawfully, fairly and transparently and limited to what is necessary to achieve the study objectives.

#### Data storage and access control

All study data will be stored in Castor EDC, a GDPR-compliant EDC system. Each participant will be assigned a unique study identification code that is not derived from personal identifiers. The key linking study IDs to patient identities will be stored securely at the participating centre and safeguarded by the local investigator. The coordinating investigator and principal investigator are authorised to enrol participants, manage the e-CRFs and export pseudonymised data for analysis. Referring gynaecologists are authorised only to complete patient-specific e-CRFs for participants from their centre. In their absence, a delegated physician from the same medical centre may complete the e-CRF. Pseudonymised datasets will be exported to Excel and SPSS for statistical analysis. Pseudonymised research data from e-CRFs and questionnaires will be stored on a secure, institutionally managed online drive with restricted access for members of the SEIC Study Group.

#### Data sharing

After completion of the primary analyses, anonymised datasets may be shared with collaborating research centres on reasonable request and approval by the study investigators, in accordance with applicable data-protection regulations.

#### Pathology data and biological material

In the Netherlands, pathology data are registered in the Dutch Nationwide Pathology Databank (PALGA). Pathology results from referring centres will be entered into the e-CRF. Access to PALGA’s internal database by members of the research team will only occur if participants have provided explicit consent and if necessary for completeness of data. For international participating centres, e-CRFs will be completed by the treating clinician or pseudonymised pathology reports will be securely transmitted to the coordinating investigator. Additional diagnostic analyses (eg, immunohistochemistry, mutation analysis, MSI testing) may be performed if not previously available. Results and images will then be stored in the secure internal pathology database of Erasmus MC. Pathology specimens are coded using original pathology (T-)codes and stored in accordance with routine clinical practice for a minimum of 10 years. Use of residual material for additional analysis will only occur if participants provide consent. Participating centres are strongly encouraged to involve pathologists with expertise in gynaecological pathology. Whenever feasible, cases will undergo review by a gynaecological pathologist with expertise in serous endometrial neoplasia. If this expertise is not available in the participating centre or within the regional gynaecological oncology network, central pathology review will be performed by the coordinating research team of the Erasmus Medical Center. Any diagnostic revisions following expert review will be documented in the registry. Furthermore, raw histopathological and molecular data will be collected to facilitate reassessment and future reclassification where necessary. The T-code is not directly linked to hospital patient identifiers and can only be linked to study IDs by authorised pathologists.

#### Withdrawal and data retention

If a participant withdraws from the study or is lost to follow-up, the reason will be recorded in the e-CRF. Data collected up to the point of withdrawal may be retained and analysed unless the participant explicitly requests deletion, in accordance with GDPR. Study data will be stored for a minimum of 15 years after study completion.

### Statistical analysis

Baseline characteristics, treatment details and outcome measures will be analysed using descriptive statistics. Continuous variables will be summarised using means and SD or medians and IQRs, as appropriate. Categorical variables will be presented as frequencies and percentages. Longitudinal QoL scores will be summarised descriptively over time. Comparisons between groups, if applicable, will be performed using the χ² test or Fisher’s exact test for categorical variables and the unpaired T-test or Mann-Whitney U test for continuous variables, depending on data distribution. If subgroup analyses are feasible, patients will be stratified according to the extent of surgical treatment (eg, complete surgical staging vs hysterectomy with bilateral salpingo-oophorectomy only). PFS and OS will be estimated using the Kaplan-Meier method, and differences between groups will be assessed using the log-rank test. Survival analyses will use the date of histopathological diagnosis as the index date. Univariate Cox proportional hazard regression analyses will be performed to explore potential predictors of survival outcomes. Multivariable Cox regression analysis will be conducted only if the number of events allows reliable modelling. Results will be reported as HRs with 95% CIs. All statistical analyses will be performed using the SPSS, V.25.0. A two-sided p<0.05 will be considered statistically significant.

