**Trial registration number:**

NCT06677242.

STRENGTHS AND LIMITATIONS OF THIS STUDYThis prospective multicentre registry is specifically designed for patients with serous endometrial intraepithelial carcinoma (SEIC) and equivalent non-invasive serous endometrial lesions.Standardised collection of clinical, pathological, molecular and patient-reported outcome data enables comprehensive long-term follow-up.The observational design reflects real-world clinical practice across academic and non-academic centres.Owing to the rarity of SEIC, the anticipated sample size is limited, which may restrict statistical power for subgroup and multivariable analyses.Central pathology review is strongly recommended but not mandatory, and treatment allocation is not protocol-mandated, introducing potential diagnostic heterogeneity and confounding by indication.

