19^ The impact of surgical staging on SEIC survival outcomes remains uncertain due to limited data. Lymph node sampling, especially lymph node dissection, lacks clear evidence, leaving ambiguity about SEIC metastasis to pelvic or para-aortic/paracaval nodes. Bilateral sentinel lymph node sampling has also been recommended, as sentinel lymph node procedures are increasingly performed for endometrial carcinomas.^12^ We propose that superficial intraepithelial carcinoma may disseminate via the fallopian tubes into the peritoneal cavity. Consequently, the necessity of lymph node sampling or dissection in SEIC treatment remains uncertain. In our recently published retrospective cohort study, 23 patients diagnosed with SEIC were evaluated, revealing no evidence of disease dissemination at the time of surgery. Over a follow-up period of nearly 3 years, no disease recurrences have been documented.^20^ Since complete staging did not detect any metastasis in this study it might be safe to omit standard staging procedure and to perform a simple hysterectomy with peritoneal washings and peritoneal biopsies (including biopsy of the infracolic omentum). Therefore, the primary objective of this study is to establish an international registry and longitudinally monitor patients diagnosed with SEIC, thereby contributing to the augmentation of knowledge and improvement of treatment strategies. This study establishes a registry for longitudinally monitoring of patients with non-invasive serous carcinomas/SEIC. By evaluating surgical and systemic treatments, we aim to enhance knowledge and refine treatment strategies, ultimately impacting patient survival outcomes and quality of life (QoL). Because the terminology may be further consolidated in the coming years, this study uses the combined term ‘non-invasive serous carcinoma’ including SEIC and FIGO IC serous carcinomas, and includes all lesions meeting the pathological criteria for SEIC, regardless of diagnostic nomenclature. This ensures compatibility with current and future classification systems. We hypothesise that patients with non-invasive serous carcinoma of the endometrium have a low risk of extrauterine disease and recurrence, and that less extensive surgical management may be associated with similar oncological outcomes while potentially reducing treatment-related morbidity and preserving QoL. This registry is designed to explore this hypothesis and generate evidence for future studies.

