#### Case identification and recruitment

Patients will be enrolled by the principal investigator, the coordinating investigator or the research nurse of the Erasmus Medical Center, after signed informed consent was obtained at one of the participating centres. Patients will be informed by their primary clinician (gynaecologist) and provided with a patient information brochure. If the patient is interested in participating, a hardcopy informed consent form is provided or a link to ValidSign^21^ via email will be sent, where a special PDF version of the informed consent form is available. The participant can sign this with an ‘advanced electronic signature’ with SMS verification. The digital consent form will then be downloaded to a secure drive on the Erasmus MC network for archiving. From all participants who provided written informed consent in a participating centre, the signed form will be scanned and stored digitally in the participating centre. All clinical data are prospectively collected through electronic case report forms (e-CRF) by the treating gynaecologist of the participating centre. The coordinating investigator will re-evaluate the provided data and ensure that collecting data is complete. All participants will receive an online questionnaire using a survey package in Castor Electronic Data Capture (EDC) at the time of diagnosis and during follow-up after 6 months, 2 years and 5 years of diagnosis, respectively. The survey package includes three online questionnaires: EQ-5D-5L QOL, QLQ-EN24 and QOL-C30. The estimated time needed to complete the three questionnaires is 15 min. Regarding therapy of SEIC, all treatment options are allowed (surgery, systemic therapy, radiotherapy). There will be no specific, patient-tailored recommendations regarding the given therapy. All interventions are part of regular medical treatment and are registered. The methods are all part of standard clinical care, apart from the collection of data through the questionnaires. Since this is an observational study, no interventions are performed.

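### If surgical groups are compared on follow-up quality of life, the only test named makes no stated use of the baseline score that is collected with the same questionnaires

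*Protocol article*

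**What the plan says.** The Protocol article, under Data collection, has patients complete the questionnaires "at baseline (prior to treatment, if applicable), and at 6 months, 2 years and 5 years after diagnosis". Case identification and recruitment describes one package for all time points: "The survey package includes three online questionnaires: EQ-5D-5L QOL, QLQ-EN24 and QOL-C30". Health-related QoL is a secondary outcome.

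The Introduction states a hypothesis that contrasts surgical strategies: "less extensive surgical management may be associated with similar oncological outcomes while potentially reducing treatment-related morbidity and preserving QoL". The strengths and limitations list concedes that "treatment allocation is not protocol-mandated, introducing potential diagnostic heterogeneity and confounding by indication".

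Statistical analysis has one sentence specific to QoL: "Longitudinal QoL scores will be summarised descriptively over time". A general sentence follows on comparisons between groups, to be made if applicable, and for continuous variables it names "the unpaired T-test or Mann-Whitney U test for continuous variables, depending on data distribution". On the grouping: "If subgroup analyses are feasible, patients will be stratified according to the extent of surgical treatment". Regression appears only for survival outcomes (Cox models), and the two-sided 5% threshold is stated without restriction to any outcome.

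**The concern.** QoL scale scores are continuous, and the Introduction's QoL hypothesis is a contrast between less and more extensive surgery. If that contrast is tested, the article offers one tool, a two-sample test, and does not say that the baseline score enters it.

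In a non-randomised cohort this matters in two ways.

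- **Bias.** If frailer patients with lower QoL are steered to limited surgery, a crude follow-up comparison would make limited surgery look worse and could hide the benefit the registry hopes to see. If selection runs the other way, it could create an apparent benefit.
- **Precision.** Variation between patients that the baseline score could explain stays in the error term of an already small cohort.

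The issue is separate from missing questionnaires, because it would remain with complete data. The information needed to reduce it is already being collected.

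**Working it through.** The article gives no QoL effect, correlation, group split or power figure, so there is no stated result to reproduce. What follows is an illustration.

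**Inputs**
- N: about 100 eligible × 75% consent = 75 (Sample size calculation).
- Two-sided alpha 0.05 (Statistical analysis).
- Assumed: split 38/37 or 22/53; baseline to follow-up correlation ρ = 0.3, 0.5, 0.7; baseline gap b = 0.25 or 0.5 SD; for power, a true difference of 0.5 SD. Scores are in units of the within-group SD.

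**1. False positives of the crude test.** Suppose surgery has no effect and follow-up = ρ × baseline + noise. The expected crude follow-up difference is ρ × b, with standard error √(1/n₁ + 1/n₂). For 38/37 this is √(1/38 + 1/37) = 0.231. With ρ = 0.5 and b = 0.5 the spurious difference is 0.25 SD and the noncentrality is 0.25/0.231 = 1.08. The noncentral t with 73 df then gives P(p < 0.05) = 19%.

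| b | ρ | spurious difference (SD) | 38/37 | 22/53 |
|---|---|---|---|---|
| 0.25 | 0.3 | 0.075 | 6% | 6% |
| 0.25 | 0.5 | 0.125 | 8% | 8% |
| 0.25 | 0.7 | 0.175 | 12% | 10% |
| 0.5 | 0.3 | 0.15 | 10% | 9% |
| 0.5 | 0.5 | 0.25 | 19% | 16% |
| 0.5 | 0.7 | 0.35 | 32% | 28% |

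Under this model, analysis of covariance (ANCOVA) on baseline rejects in about 5%. That follows from how the model is built.

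**2. Precision.** Adjustment multiplies the residual variance by 1 − ρ², a cut of 9%, 25% or 49%. Power uses the noncentral t with effect 0.5/√(1 − ρ²) and 72 df.

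| split | unadjusted | ρ = 0.3 | ρ = 0.5 | ρ = 0.7 |
|---|---|---|---|---|
| 38/37 | 57% | 61% | 69% | 85% |
| 22/53 | 49% | 53% | 61% | 78% |

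For 38/37 the 95% CI half-width is 1.99 × 0.231 = 0.46 SD unadjusted, and 0.46 × √0.75 = 0.40 SD at ρ = 0.5.

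**3. How much of that gain survives lost baselines.** At a fixed split, variance is proportional to (1 − ρ²)/n. The adjusted analysis therefore beats the crude one on all 75 only if more than 75 × (1 − ρ²) patients have a pre-surgery form: about 68, 56 or 38 at ρ = 0.3, 0.5 or 0.7.

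**4. Would change scores be enough?** Under the model in step 1 the expected difference in change is −(1 − ρ) × b, with SD √(2(1 − ρ)). For b = 0.5 and 38/37 the unpaired t-test on change rejects in 24%, 19% and 13% at ρ = 0.3, 0.5 and 0.7.

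**5. A different null.** Suppose instead that the groups differ by a stable 0.5 SD in underlying QoL, measured with error at both times (simulation, 20,000 runs, 38/37). The crude test rejects in 57%. ANCOVA keeps a bias of (1 − ρ) × 0.5 = 0.25 SD at ρ = 0.5 and 0.15 SD at ρ = 0.7, rejecting in 22% and 14%. The change-score test is unbiased and rejects in 5%.

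**The case against.** The strongest case against is that the flawed analysis is never actually announced. A reader might infer that unadjusted tests of follow-up QoL are planned and that their results will be read as effects of surgery. The documents do not support that. The test sentence is general and conditional, it covers variables such as age and body mass index as well, and stratification by surgery is conditional on feasibility. The only QoL-specific sentence is descriptive. An unpaired test on change from baseline would also fit the wording. The article calls its analyses primarily descriptive, presents the registry as exploratory, and discloses confounding by indication. All of this stands, and it is why the point is conditional.

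It is also fair that a condensed article may leave a secondary QoL model to a fuller document, so the lack of a model is not in itself an error. What remains is that the article does name a method for group comparisons, makes no exception for QoL, and that method suits this contrast poorly.

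Two further objections stand in part. First, ANCOVA is not a guaranteed correction: step 5 shows residual bias when groups differ stably and QoL is measured with error. But the crude comparison is worst in that scenario, and step 4 shows that change scores can mislead too. This argues for showing more than one analysis. Second, 75 is optimistic. It needs every Dutch consenter to fall into one of two groups although several procedures are listed, to have a pre-surgery baseline, and to return each follow-up form. Baseline is pre-treatment only where applicable, so the precision gain may be much smaller than in step 2, or absent.

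Disclosing confounding as a limitation does not reduce it when the relevant covariate is at hand.

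**Conclusion.** The concern holds in conditional form. If surgical groups are compared on follow-up QoL, the only named method makes no stated use of the baseline score, and a crude comparison may then show pre-treatment differences as apparent effects of surgery.

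The illustrative size is a false-positive rate of about 6% to 32% instead of 5%, and 9% to 49% of residual variance left unexplained. It rests on 75 patients in two groups, a gap of 0.25 to 0.5 SD, ρ of 0.3 to 0.7, and group acting on follow-up only through baseline. Only the 75 comes from the article. Two conclusions do not depend on the exact values: a crude follow-up comparison is hard to defend in non-randomised groups when baseline scores exist, and no single baseline method removes all the confounding.

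This should be corrected. It concerns a secondary outcome and does not affect the progression-free survival analysis. Confidence is medium, because the text leaves open whether the comparison will be made at all.

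**What to change.** In Statistical analysis, add one of two statements.

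- **If groups will be compared on QoL:** any between-group comparison of follow-up QoL will use a linear model at each of 6 months, 2 years and 5 years, with surgical group and the same scale's baseline score as covariates. Only baseline questionnaires completed before the primary surgery count. Report the adjusted mean difference with 95% CI, and give the change-from-baseline and crude comparisons as sensitivity results, because ANCOVA does not fully remove confounding in non-randomised groups. Keep the two-sample tests for variables without a baseline value.
- **If not:** QoL stays descriptive, with no between-group tests.

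The cost is one or two sentences and a standard SPSS model, with no new data, visits or patients, and one degree of freedom per model. The real downside is that patients whose baseline form was completed after surgery drop out of the adjusted contrast, possibly unevenly between groups. Their number should be reported per surgical group. Adjustment removes confounding only as far as measured baseline QoL captures it, and the report should say so.

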## Introduction

 Serous endometrial intraepithelial carcinoma (SEIC) (Tumor characteristics were coded according to the International Classification of Diseases for Oncology (ICD-O) code 8441/2) is defined as a non-invasive lesion of the endometrial epithelium, replacing the native surface of the endometrium.^1
2^ A p53 mutation is often present, diagnosed through immunohistochemistry, which classifies SEIC in the p53 mutant endometrial tumours.^3
4^ Despite its non-invasive nature, SEIC exhibits malignant potential and poor prognosis, with documented cases of extrauterine dissemination even at presentation.^5–8^ Published case series and a recently published review have recommended performing surgical staging as primary treatment.^1
7
9–12^ In the Netherlands, clinical management varies from therapeutic hysteroscopy to surgical staging procedures.^13^ International guidelines lack specific recommendations for managing SEIC as a distinct entity. Although SEIC is currently defined as a non-invasive serous lesion, it is increasingly considered part of the serous, p53-mutated endometrial tumours rather than as a distinct entity.^12
14
15^ The collaborative guideline for managing patients with endometrial carcinoma by the European Society of Gynaecological Oncology, European Society for Radiotherapy and Oncology, and European Society of Pathology positions SEIC-equivalent FIGO IC (stage IC according to the International Federation of Gynecology and Obstetrics staging system) serous lesions in a grey zone of ‘uncertain risk’ due to insufficient outcome data, underscoring the lack of consensus and the evolving nature of its classification. This guideline has no explicit management recommendations for the uncertain risk category.^15^ The National Comprehensive Cancer Network guideline in the USA advises surgical staging and adjuvant therapy for all serous carcinoma FIGO 1A or higher, without a distinct section dedicated to SEIC management.^16
17^ Surgical staging, whether performed via laparotomy or minimally invasive techniques, entails a comprehensive procedure associated with recognised risks of complications.^18

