## Methods and analysis

### Study objectives

The aims of this registration study include: (1) To establish and maintain a prospective observational registry of patients diagnosed with SEIC and equivalent non-invasive serous tumours. (2) To systematically collect clinical, diagnostic, tumour, treatment and outcome data in patients with SEIC. (3) To evaluate the association between the extent of surgical treatment, the use of adjuvant therapy and progression-free survival (PFS).

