#### Exclusion criteria

Participants are not eligible for inclusion if they meet one of the following criteria:

Any diagnosis other than a non-invasive serous intraepithelial endometrial lesion, including:Endometrioid carcinoma.Clear-cell carcinoma.Serous carcinoma with invasion.Carcinosarcoma.Endometrial hyperplasia or endometrial intraepithelial neoplasia.Cases in which histopathology shows (also) myometrial or stromal invasion, even if previously labelled SEIC.

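### Grouping patients by the surgery performed, with no planned procedure among the listed variables, can make limited surgery look safer if operations are extended when disease is seen

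*Protocol article*

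**What the plan says.** - **Grouping.** Statistical analysis makes the grouping conditional on feasibility: "patients will be stratified according to the extent of surgical treatment (eg, complete surgical staging vs hysterectomy with bilateral salpingo-oophorectomy only". The groups are then compared on PFS and OS by log-rank test and univariate Cox regression. Multivariable Cox follows only if there are enough events.
- **Data.** Collected variables lists the surgical procedure by type, and the list runs on to "staging procedure, cytoreductive surgery), perioperative findings (dissemination of disease and FIGO stage of disease". The planned procedure and a reason for changing it are not among the listed items.
- **Aim.** The third item under Study objectives is "To evaluate the association between the extent of surgical treatment, the use of adjuvant therapy and progression-free survival (PFS".
- **Hypothesis.** The Introduction expects that "less extensive surgical management may be associated with similar oncological outcomes".
- **Eligibility.** The exclusion that concerns spread is "Cases in which histopathology shows (also) myometrial or stromal invasion, even if previously labelled SEIC". Disease outside the uterus is not excluded, and the Introduction describes the lesion as one "with documented cases of extrauterine dissemination even at presentation".
- **Disclosed limitation.** The strengths and limitations box mentions confounding by indication in general terms, because treatment is not allocated by protocol.

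**The concern.** The hypothesis is about a strategy, namely choosing less surgery. The groups are formed from what was done. If a surgeon who planned a hysterectomy with salpingo-oophorectomy sees disease and extends the operation, that patient is recorded under the larger procedure. A patient planned for staging with the same finding stays where she was. Group membership is then partly a result of prognosis, and patients with visible disease move in one direction only, out of the limited group. This mechanism favours the study's own hypothesis. Adjusting for variables known before the operation does not remove it, because the sorting happens during the operation.

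There is a related problem of meaning. A lesion found by chance in a hysterectomy specimen, with no further surgery, would count as hysterectomy only, although nobody chose limited surgery for this diagnosis. The documents give no basis for a size or direction of that effect.

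At stake is the only surgical contrast named for the third aim, and it is the one readers would use when judging whether staging can be omitted.

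**Working it through.** The article gives no event rate, effect size or power for this comparison, so there is no stated figure to reproduce. The check asks how large a false difference the grouping could create when surgery has no effect.

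**Inputs from the article**
- About 100 eligible patients × 75% consenting = 75 (Sample size calculation).
- Dissemination at surgery in the investigators' retrospective cohort: 0 of 23 (Introduction).

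**Assumptions, not in the article**
- 30 patients planned for limited surgery and 45 for staging, with visible disease equally common in both.
- Five-year PFS-event risk 5% without and 50% with visible disease.
- Every limited-plan patient with visible disease is converted and counted in the staging group.

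**1. What 0 of 23 allows.** One-sided 95% upper limit: 1 − 0.05^(1/23) = 12.2%. Two-sided: 1 − 0.025^(1/23) = 14.8%. Rates of 0%, 2% and 6.7% are all compatible with it.

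**2. Visible disease 6.7% (5 of 75: 2 planned limited, 3 planned staging)**
- By plan: limited (28 × 0.05 + 2 × 0.50)/30 = 2.4/30 = 8.0%; staging (42 × 0.05 + 3 × 0.50)/45 = 3.6/45 = 8.0%.
- By procedure performed: limited 28 × 0.05/28 = 5.0%; staging (42 × 0.05 + 5 × 0.50)/47 = 4.6/47 = 9.8%.
- False risk ratio, staging over limited: 9.8/5.0 = 1.96.

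**3. Visible disease 2% (0.6 and 0.9 expected patients)**
- By procedure performed: limited 5.0%; staging (44.1 × 0.05 + 1.5 × 0.50)/45.6 = 2.955/45.6 = 6.5%.
- False risk ratio 1.30.

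**4. When the ratio is 1.0**
- No visible disease: both groups 5.0%.
- Visible-disease cases kept out of both groups, at 6.7%: 28 × 0.05/28 = 5.0% against 42 × 0.05/42 = 5.0%.

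**5. Frailty acting the other way.** PFS counts death from any cause. Suppose patients planned for limited surgery carry 5 extra percentage points of other-cause death.
- At 6.7%: limited 28 × 0.10/28 = 10.0%; staging (42 × 0.05 + 3 × 0.50 + 2 × 0.55)/47 = 4.7/47 = 10.0%; ratio 1.0 (offset).
- At 2%: limited 10.0%; staging (44.1 × 0.05 + 0.9 × 0.50 + 0.6 × 0.55)/45.6 = 2.985/45.6 = 6.5%; ratio 0.65 (reversed).

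**6. Sensitivity to the assumptions.** A second model uses a 1:1 planned split, no frailty and HR = ln(1 − risk limited)/ln(1 − risk staging). Here a value below 1 favours limited surgery.

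| Visible disease | Half converted, 30% risk if visible | All converted, 60% risk if visible |
|---|---|---|
| 0% | 1.00 | 1.00 |
| 2% | 0.91 | 0.69 |
| 5% | 0.82 | 0.47 |
| 10% | 0.73 | 0.32 |
| 14.8% | 0.68 | 0.24 |

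**7. Scope for adjustment.** At 6.7%, expected events are 75 × 0.08 = 6.0, so the conditional multivariable model is unlikely to be run.

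**The case against.** A reader might infer that the limited-surgery group is bound to be cleared of its worst patients and will look safer than it is. The documents do not support that much.

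- No section says that surgery is extended when disease is seen. It is a reasonable inference, helped by cytoreductive surgery being a listed procedure type.
- The only rate in the article is 0 of 23, at which this bias is nil. At 2% visible disease the model converts 0.6 of a patient.
- Cytoreductive surgery is listed separately from the staging procedure, so the example contrast need not put those patients in the staging arm. If all visible-disease cases fall outside both arms, the false ratio disappears (step 4).
- Selection of frailer patients for limited surgery would push all-cause PFS the other way (step 5).

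These arguments stand, and they limit the claim to what can happen.

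Other defences stand in part. The comparison is conditional, its groups are given as an example, and the study calls itself primarily descriptive. It is still the only surgical grouping named for the third aim, and a 5% significance threshold is attached. Confounding by indication is disclosed, but the disclosure changes nothing in the analysis. Dissemination at operation is already recorded, so a restricted analysis is possible; it does not recover what was intended. Route to diagnosis may be partly derivable from the biopsy and specimen data. The article condenses a fuller protocol and the case report form is not shown, so the form may already hold the planned procedure. The grouping by treatment extent is nonetheless stated outright.

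**Conclusion.** The point holds in a limited form. The surgical groups are defined by treatment received, no planned procedure appears among the listed variables, and patients with extrauterine disease can enrol. If operations are extended on seeing disease and those patients are counted as staged, limited surgery can look safer than the strategy is.

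Under the main assumptions the false risk ratio is about 1.3 at 2% visible disease and about 2.0 at 6.7%. It is 1.0 if no disease is seen or if such cases stay out of both groups. The risks, the 30/45 split and full conversion are assumptions, and the net direction is not fixed once frailty selection is allowed for. This is a cheap improvement to an exploratory comparison; it does not show that the result will be biased.

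**What to change.** 1. In the case report form, record the procedure planned before the operation, the reason for any change, and the route to diagnosis (before definitive surgery, or incidental in a hysterectomy specimen), unless these are already there.
2. In Statistical analysis, define the surgical comparison by planned procedure among patients diagnosed before definitive surgery. Keep performed extent as a secondary classification.
3. Report incidental, converted and cytoreductive cases separately, and state how cytoreductive cases are handled in any two-group contrast.
4. Add a sensitivity analysis limited to patients without visible dissemination, using the perioperative findings already collected.

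**Cost.** A few form fields, a short addition to the analysis section, and a smaller main contrast, because incidental diagnoses leave it. Planned groups remain open to confounding by indication, since imaging and performance status can influence the plan; the change removes only the sorting that happens during surgery. It is best made early: Study status puts recruitment from May 2026 to April 2031, and intent that was not recorded at the time is hard to reconstruct. Nothing here alters how patients are treated.
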